##### Kidscreen-27 (KIDSCREEN Group, 2006)

Kidscreen-27 is a questionnaire that evaluates the generic health-related quality of life (HRQol) in 6- to 18-year-old children. The Kidscreen-27 items are derived from the Kidscreen-52 questionnaire. There are two versions, one completed by parents (or primary caregivers) and the other by children. Children evaluate the subjective perception of their well-being during the last week. Kidscreen-27 comprises five domains: “Physical well-being,” “Psychological well-being,” “Autonomy and parents,” “Social support and peers,” and “School environment”. The responses are scored on 5-point Likert scales for frequency (never to always) or intensity (not at all to extremely). Kidscreen-27 has been translated into 36 languages. Kidscreen-27 scores are converted to *T*-values (standardized mean = 50, standard deviation = 10). Higher scores indicate good HRQol and well-being [70].

##### Parental Quality of Life and Developmental Disorder in their children (Par-DD-Qol [13];)

The Par-DD-Qol is a parent-completed 17-item questionnaire to assess the impact of their child’s chronic disabilities on the parental quality of life (Qol). It is particularly adapted to parents of children with neurodevelopmental disorders, because these are chronic conditions that impact the parents’ Qol. The questionnaire includes several dimensions: “Emotional,” “Daily Disturbance,” and “Global Qol.” It is adapted from the Par-ENT-Qol [13] used in the general population with chronic ear, nose, and throat (ENT) infections. Responses are scored on a 5-point Likert scale (not at all to very much). Several studies ([8]; Raysse, 2011) showed a reliability coefficient higher than 0.82 (Cronbach’s alpha) for each dimension. A score below 40 indicates “no impact” on the parents’ Qol, a score between 40 and 57 a “moderate impact,” and a score higher than 57 a “high impact.”

##### Behavioral Rating Inventory of Executive Function (BRIEF; Gioa, Guy & Kentworthy, 2000)

BRIEF is a parent- or a teacher-completed 86-item inventory to assess the executive functioning of 5- to 18-year-old children at home and in school environments using a three-point scale for frequency (never to always). The instrument includes eight scales that measure executive functioning: initiate, work memory, plan/organize, organization of materials, and monitor (forming the metacognition index [MI]), and inhibit, shift, and emotional control (forming the behavioral regulation index [BRI]). The BRI assesses the ability to use appropriate inhibitory control to shift cognitive sets and modulate emotions and behaviors. The MI assesses the ability to use working memory to initiate, plan, and sustain future-oriented problem solving [61]. BRIEF includes two validity scales (Negativity and Inconsistency of responses) to identify the parents’ response styles and to validate the questionnaire quality. A *T*-score of 65 indicates clinically significant executive function impairment. Gioia et al. (2000) reported that the BRIEF reliability coefficient ranges from 0.80 to 0.97 for the two forms (Parent and Teacher), except for two scales (“Initiate” and “Shift”).

##### Parenting Stress Index, 4th edition, short form (PSI-4-SF, [1])

The PSI-4-SF is a 36-item parent-completed questionnaire to measure the parental stress and to detect difficulties in the parent-child dyad. This is defined as a state of psychological malaise in parents related to the parent-child relationship. Responses are provided on a 5-point Likert scale (totally disagree to totally disagree). The questionnaire includes three subscales (“Parental distress,” “Dysfunction in parent-child interactions,” and “Difficulties in children”) to assess the factors that may influence the level of stress experienced by parents in their relationship with their child. The first subscale “Parental distress” allows measuring the distress experienced by parents in the exercise of their role. The second subscale “Dysfunction in parent-child interactions” measures the parents’ satisfaction of their relationship with their child and whether the child meets their expectations. The third subscale “Difficulties in children” assesses the parents’ degree of distress due to their child’s difficult behavior. A score between the 85th and 89th percentile indicates high stress level, and a score ≥ 90th percentile is clinically significant. Abidin [2] reported a reliability coefficient of 0.84 (test-retest, 6 months) and internal consistency coefficient of 0.95 (Cronbach’s alpha) for the total score. The three subscales have internal consistency coefficients of 0.90, 0.89, and 0.88, respectively. PSI-4-SF is strongly correlated with the original version of the PSI-4, with a correlation coefficient of 0.98 for the Total Stress Scale.

##### Beck Depression Inventory-II (BDI-II; Beck, Steer & Brown, 1996)

The BDI-II is the most popular screening instrument for depression in adolescents and adults. It is a 21-item self-report questionnaire that examines the behavioral, emotional, somatic, and cognitive symptoms of depression in the past 2 weeks. Each item is rated on a 4-point Likert scale (ranging from 0 to 3), reflecting the symptom severity. Scores from 0 to 13 indicate “Minimal depression,” scores from 14 to 19 “Mild depression,” scores from 20 to 28 “Moderate depression,” and scores higher than 29 indicate “Severe depression.”

Wang and Gorenstein [92] reported a mean alpha coefficient of 0.9 (ranging from 0.83 to 0.96) and excellent coefficients of retest reliability (0.73 to 0.96). The BDI-II is valid in different cultures and presents strong psychometric properties (Beck, Steer & Brown, 1996).

##### Hierarchical Personality Inventory for Children (HiPIC, Mervielde & De Fruyt, 1999)

HiPIC is a 144-item parent-completed questionnaire to obtain a profile of the personality of 6- to 12-year-old children according to a five-factor model. Responses are scored on a 5-point Likert scale (from “Very untypical” to “Very typical”). Five personality dimensions are assessed: “Emotional Stability,” “Extraversion,” “Benevolence,” “Conscientiousness,” and “Imagination.” HiPIC is scored on 18 facets composed of 8 items/each that are summed and averaged to obtain the dimensions. The “Extraversion” dimension includes positive emotionality, energy in children, and ease in social situations. The “Emotional stability” dimension assesses negative emotions and reactions toward their environment. The “Conscientiousness” dimension measures the determination and drive to achieve a goal. The “Benevolence” dimension evaluates agreeableness, attitude in relationships, and ability to empathize. The “Imagination” dimension represents creativity, curiosity, and openness to new experiences. Mervielde and De Fruyt (1999) reported a reliability coefficient of 0.70 (Cronbach’s alphas) for each domain and facet.

The objective of the inclusion of HiPIC is to better understand personality profile in children with ADHD and emotion dysregulation. Currently, there is a lack of studies in personality traits in children with ADHD and emotion dysregulation.

In this trial, we did not expect to assess variation of personality traits (HiPIC), but just better understand the overall functioning of children with ADHD and emotion dysregulation and to assess whether personality profiles would predict treatment response. As the HiPIC is a relatively long questionnaire and as personality is considered stable in the study’s time frame, we included it at T1 rather than at baseline.

##### Children’s Global Assessment Scale (C-GAS, [75])

C-GAS is a numeric scale to assess the general functioning in 4–16-year-old children. This scale is used and completed by mental health clinicians. A clinician interviews the child, parents, and school staff to assess the child’s global functioning. C-GAS is adapted from the Global Assessment Scale for adults. Scores are divided in ten categories that range from “Extremely impaired” (1–10) to “Doing very well” (91–100).

##### Schedule for Affective Disorders and Schizophrenia for School-aged Children, Present and Lifetime version (K-SADS-PL [42];; French version Mouren-Siméoni & al., 2002)

K-SADS-PL is a semi-structured diagnostic interview to assess all current and lifetime DSM-IV Axis I mental disorders in 6–18-year-old children. K-SADS-PL is administrated by trained mental health clinicians (master level).

#### Other measures

Demographic information was obtained thanks parents during inclusion visit (T0). For all children, clinical investigator collects gender, age, and school level, and for parents, marital status, academic level, socioeconomic status, and psychiatric/somatic pathologies. Pharmacological treatments were recorded at each visit, because introduction or interruption of medication or modification of posology may influence research outcomes. Indeed, ADHD usual treatment effectively reduces emotional dysregulation [46, 84, 86, 97]. Likewise, life events (e.g. move, death or illness of a family member…) were also listed at each visit, as they could have an impact on results.

### Plans to promote participant retention and complete follow-up {18b}

Evaluation visits will be scheduled at the intervention end (T2) and at month 6 post-intervention (T3) (see Table 1). Two weeks before the intervention end, the psychologist will propose to parents an appointment for the T2 visit. For the appointment of the follow-up visit (T3), families will be contacted by telephone by the psychologist. For families difficult to reach, several telephone calls may be made. The child’s referring psychiatrist will be also contacted to improve data collection (e.g., he/she might call the family to emphasize the importance of completing the questionnaires, refer family to the psychologist after consultation…).

For families unable to attend the visit (health problems…), it might be exceptionally decided to complete the questionnaires and the case report form (CRF) during a telephone conversation. This will be indicated in the CRF.

If parents decide to interrupt their trial participation, the investigator will contact them to know whether they agree to complete the final questionnaires.

To promote participant retention during the program, families will be contacted by telephone in case of absence during two sessions.

### Data management {19}

For each participant, data will be reported in a CRF, first in paper format and then electronically. The used software, Capture System, complies with the FDA recommendations on computerized systems for managing clinical trials.

The data manager will perform additional computerized consistency tests to detect the presence of non-standard, missing, aberrant, or incoherent data. These tests will be executed regularly during the participants’ recruitment and monitoring. Each identified incoherence will be the subject of a request for clarification to the researcher.

Data will be saved by the Clinical Research and Epidemiology Unit (CREU) of Montpellier Hospital and will be stored in ASCII type format.

### Confidentiality {27}

Data will be collected in the CRF only by the research psychologist. Each CRF will be anonymized to respect the participants’ confidentiality.

### Plans for collection, laboratory evaluation, and storage of biological specimens for genetic or molecular analysis in this trial/future use {33}

This trial will not involve collection and storage of biological specimens for genetic or molecular analysis.

## Statistical methods

### Statistical methods for the primary and secondary outcomes {20a}

An intention-to-treat approach will be used to analyze the primary and secondary data from the trial. Participants will be analyzed in their randomization arm and cannot change group during the study.

The primary outcome measure is the changes of the “Aggressive behavior” sub-score between T1 (baseline) and T3 (month 6 post-intervention). A *Z* test will be used to compare the changes of the primary (between T1 and T3) and secondary outcomes (between T1 and T2/T3) in the CBT group and TBI group. In the case of group non-comparability, a multivariate model by linear regression could be carried out to take into account the potential confounding bias.

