#### Theater-based intervention (TBI)

TBI is a role-play activity that is part of our day-care activity schedule. The TBI group participates in 1-h sessions (one per week; 15 in total) led by two mental health workers (nurse or special educator) trained in the management of behavioral disorders, ADHD, and experienced in theater-play. The TBI sessions are not based on a specific program, and their content was developed from existing acting techniques already used in psychiatry (Héril and Mégrier, 2005; Alix and Renard, 2015).

The program objectives are to develop self-control and self-confidence skills, prosocial skills, and appropriate expression of emotions through role-play exercises. During the program, children are also trained in other competences, such as impulsivity control.

Each session includes structured and tailored activities:
A warm-up phase around active group exercises: children are in motion, while learning how to regulate their impulsivity;An individual phase with exercises of improvisation, expression of emotions, and memory;A phase of game in pairs that includes several exercise types: role-playing around everyday life, games where children learn how to use prosocial skills and how to work in teams.A fun and collective play time that lasts 5 min. This time allows children to let off steam.A quiet time: at the session end, children enjoy a time of relaxation or meditation. This moment allows children to refocus on themselves and to learn techniques to manage their emotions. These exercises help to increase physical self-control that can promote better impulse control in children with ADHD [37].

During each session, the program includes sensory games, movement/space games, imitation activities, self-control games, and emotion expression activities.

Each session is adapted according to the individual needs of the children in the group and their age.

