### Sample size {14}

As ED in children with ADHD has been only recently studied, it is difficult to find literature data for calculating the number of subjects required (particularly for assessing the changes in the “Aggressive behaviors,” “Anxiety/Depression,” and “Attentional Problems” scores of the CBCL scale).

The study by Masi et al [54]. reported a change in the “Aggressive behavior” score of the CBCL from 68.3 to 65.5 in the context of the non-comparative evaluation of an intervention similar to the one assessed in the present trial. The standard deviation of the score at the baseline was 5.4.

By making the reasonable assumption of a slightly more effective intervention than what reported by Masi et al [55]., a CBCL score of 65 in the intervention group and 69 in the control group, with a common standard deviation of 5.5, can be expected at month 6 post-intervention. To highlight such a difference with a power of 80% and an alpha risk of 5%, 31 subjects per group need to be included. By increasing this number by 10% to take into account participants lost to follow-up, the total number of subjects to be included in the study is 68 (34 per group).

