## Assignment of interventions: allocation

### Sequence generation {16a}

After verification of the eligibility criteria, family’s information, and consent signature, each participant will be randomized. Intervention allocation will be done using a computer-based random number generator. Randomization will be performed as soon as the number of participants is reached to start a session (one CBT group and one TBI group) with a 1:1 ratio.

Randomization will be stratified by school level (primary vs middle school) and severity of psychopathological disorders using the CBCL A-A-A score. Children will be divided in groups according to their school level (< 11 years, and 11–13 years of age).

The investigator in charge of the study assessments is blinded to the group allocation.

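### Both arms are treated in therapy groups, but the Z test and the 31-per-arm sample size assume independent children, so the 5% error rate and 80% power hold only if outcomes do not correlate within groups

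*Protocol article*

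**What the plan says.** Sequence generation {16a} describes allocation in waves: "Randomization will be performed as soon as the number of participants is reached to start a session (one CBT group and one TBI group"). Intervention description {11a} gives each arm 15 weekly one-hour sessions led by two staff. For the theatre arm it adds: "Each session is adapted according to the individual needs of the children in the group and their age". The discontinuation criteria {11b} and the post-trial care section {30} recognise that one child's aggression can disrupt the group.

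Sample size {14} expects "a CBCL score of 65 in the intervention group and 69 in the control group, with a common standard deviation of 5.5", and concludes: "To highlight such a difference with a power of 80% and an alpha risk of 5%, 31 subjects per group need to be included". The only allowance made is "By increasing this number by 10% to take into account participants lost to follow-up", after which "the total number of subjects to be included in the study is 68 (34 per group").

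Statistical methods {20a} states that a Z "test will be used to compare the changes of the primary (between T1 and T3) and secondary outcomes" between the arms. The only other model named, there and in {20b}, is a linear regression for confounding if the arms turn out not to be comparable. The article mentions no ICC, design effect, or therapy-group or leader term.

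**The concern.** Children who spend 15 sessions together share leaders, peers and the course that their group takes. Their outcomes may therefore be more alike than those of children in different groups of the same arm. The Z test divides the arm difference by a standard error that ignores this. With positive within-group correlation that standard error is too small, the confidence interval is too narrow, and the nominal 5% understates the real false-positive rate. The sample size has the matching fault: its 80% power belongs to a test that is valid only without clustering.

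This bears on the single primary superiority comparison, in a trial with few therapy groups per arm. A chance difference between a handful of groups could be reported as an effect of CBT. The protocol states both the test and the size outright, so this is not a detail left open for a later analysis plan.

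**Working it through.** **1. Reproduce the plan's figure.** Inputs from Sample size {14}: difference 69 − 65 = 4, SD 5.5, alpha 5% (two-sided assumed, as one-sided would give 24 per arm), power 80%.

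- Normal formula: n = 2 × (1.960 + 0.842)² × 5.5² / 4² = 29.7, so 30 per arm.
- Two-sample t test: n = 30.7, so 31 per arm. Power at 31 is 80.4%.
- Loss allowance: 62 × 1.10 = 68.2, so 68.

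The stated 31 and 68 are reproduced with independent observations, that is, with a design effect of 1.

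**2. Add clustering.** The documents give neither group size m nor ICC. Main assumption: 5 groups of 6 per arm, ICC 0 to 0.10.

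- Design effect: DE = 1 + (m − 1) × ICC. For m = 6 and ICC 0.05, DE = 1 + 5 × 0.05 = 1.25.
- Effective sample size: 31 / DE. Here 31 / 1.25 = 24.8.
- Power: two-sample t test at that effective size, with noncentrality (4 / 5.5) × √(n/2). Here 0.727 × √12.4 = 2.56, which gives 71%.
- Type I error of the Z test: simulation of 40,000 trials, counting |Z| > 1.96 with an independent-children standard error. Repeat runs differ by a few tenths of a point.
- Group-means t test: each group's mean is one observation, 5 + 5 − 2 = 8 degrees of freedom, power by simulation.

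| ICC | DE | 31/DE | Z-test type I error | Design-effect power | Group-means t-test power |
|---|---|---|---|---|---|
| 0 | 1.00 | 31.0 | 5.5% | 80% | 69% |
| 0.01 | 1.05 | 29.5 | 6.2% | 78% | 67% |
| 0.02 | 1.10 | 28.2 | 6.7% | 76% | 66% |
| 0.05 | 1.25 | 24.8 | 8.6% | 71% | 60% |
| 0.10 | 1.50 | 20.7 | 11.9% | 63% | 53% |

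**3. Separate the sources.** The 5.5% at ICC 0 comes from using 1.96 rather than a t quantile: P(|t| > 1.96) with 58 df is 5.48%. Removing it leaves about 0.7, 1.2, 3.1 and 6.4 percentage points due to clustering at ICC 0.01, 0.02, 0.05 and 0.10. The large-sample formula 2 × (1 − Φ(1.96/√DE)), which has no such excess, gives 5.6%, 6.2%, 8.0% and 11.0%. In the last column, likewise, the fall from 80% to 69% at ICC 0 is the price of 8 degrees of freedom. Only the further fall is due to correlation.

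**4. Vary the group size.** With 4 groups of 8 per arm and ICC 0.05, the simulated type I error is 9.6% to 9.9%. With groups of 5 and ICC 0.01, DE is 1.04 and the large-sample type I error is 5.5%, which is negligible.

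**The case against.** The strongest reply is that the harm depends on two quantities the documents do not contain. The relevant ICC is for the change in a parent-rated score up to six months after the sessions end, and nothing in the article shows that it reaches 0.05 or 0.10. At 0.01 the plan is nearly right. This stands: the size can be stated only as a range, and a reader should not infer that the error rate is known to be well above 5%.

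Other tempting inferences go beyond the text:

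- **Tailored content in both arms.** Only the theatre sessions are said to be adapted to the children in the group. CBT follows a manual, with individual goals. Shared leaders and peers apply to both arms.
- **Parent groups as a second layer of clustering within arm.** The parent programme is the same for both arms, but the article does not say whether parent groups are separate by arm. If they mix arms, that layer is crossed with treatment and does not inflate the error in this way. The children's groups carry the point alone.
- **All correlation counts.** Variation shared by a whole wave, such as season, cancels because each wave supplies one group to each arm. Only group-specific correlation matters.
- **A group term would remove leader effects.** CBT is led by a psychologist and a caregiver, the theatre arm by two nurses or special educators. That difference is built into the arms, and no group term can separate it from treatment.

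It can also be said that recruitment had formally ended when the article was submitted, so restating power cannot change the design, and that an unseen analysis plan might add a group term. Neither corrects the test and power that the protocol states. Analysis waits until all visits are complete, so the test can still be changed.

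**Conclusion.** The point holds in conditional form. The design creates therapy groups in both arms, while the stated test and sample size are valid only if children's outcomes are independent within those groups. If they correlate, the Z test's true type I error exceeds 5% and a valid analysis has less than 80% power. The effect is slight at ICC 0.01 and material from about 0.05: near 8.6% error and 71% power there, and 11.9% and 63% at ICC 0.10. These figures assume 5 groups of 6 per arm, the plan's own difference and SD, and a two-sided 5% level. Power with small-sample degrees of freedom is lower, at 60% and 53% for the group-means test. The documents do not establish which ICC applies.

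**What to change.** In Statistical methods {20a}, replace the Z test with a linear mixed model of the T1 to T3 change. Include a random intercept for therapy group, Satterthwaite or Kenward-Roger degrees of freedom, and adjustment for baseline score and the two stratification factors (school level and CBCL A-A-A severity). Keep the therapy-group identifier in the database and in the imputation model of {20c}.

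A term for the wave is optional and should be weighed against the few groups. With five CBT/TBI pairs, a paired group-means test has 4 degrees of freedom and, by simulation, about 57% power at ICC 0 and 48% at ICC 0.05.

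In Sample size {14}, restate power with a design effect for the actual mean group size over ICC 0.01 to 0.10, labelled as an assumption.

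The cost is analysis wording, one identifier that the trial should be able to recover from forming its groups and recording attendance, a wider interval and a lower stated power. With few groups and a higher ICC that loss is substantial and should be disclosed. No extra patients are needed.

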### Methods in analysis to handle protocol non-adherence and any statistical methods to handle missing data {20c}

Analysis of the primary and secondary outcomes will be carried out per protocol for all families who participated in two thirds of the intervention.

For missing data, under the hypothesis of a Missing at Random (MAR) or Missing Completely at Random (MCAR) mechanism, an imputation method using the Markov chain Monte-Carlo method will be used with 15 imputation cycles. The analysis will be performed independently for each complete database and the results will be taken into account for estimating the final parameters and their standard deviations.

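### A Z test is named for change scores whose SD must be estimated from about 31 to 34 children per arm, so the two-sided error is about 5.4% to 5.5%, not 5%; a t test fits the stated sample size

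*Protocol article*

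**What the plan says.** Section {20a} (statistical methods for the primary and secondary outcomes) names the default analysis: a Z "test will be used to compare the changes of the primary (between T1 and T3"). The same test is applied to the secondary outcomes at T2 and T3. Linear regression appears in {20a} and {20b} only as a fallback for arms that turn out not to be comparable.

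Section {14} (sample size) expects "a CBCL score of 65 in the intervention group and 69 in the control group" at the six-month visit, and takes the SD to be 5.5 in both arms. It concludes that "with a power of 80% and an alpha risk of 5%, 31 subjects per group need to be included". After a 10% allowance for loss to follow-up, "the total number of subjects to be included in the study is 68 (34 per group").

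Section {20c} plans multiple imputation and a per-protocol analysis. It says that completed datasets are analysed separately and the results combined. It names no reference distribution for the pooled estimate.

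**The concern.** The normal reference distribution is exact only when the SD is known. The 5.5 in section {14} is a planning value for the month-6 score, and that section says that suitable literature data were hard to find. It cannot serve as a known SD for the change between T1 and T3. The SD will therefore come from the trial's own data, and with arms of this size the statistic follows a t distribution with 60 to 66 degrees of freedom. Comparing it with 1.96 rejects slightly too often.

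At stake is whether the primary test delivers the stated 5%. A statistic just above 1.96 would be declared significant although it is not significant at 5% by the appropriate reference.

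**Working it through.** **Inputs.** From section {14}: difference 69 − 65 = 4 points, common SD 5.5, power 80%, alpha 5%, 31 per group, 34 per group after the allowance. From section {20a}: Z test. Sidedness is not stated. Two-sided is assumed, because a one-sided 5% test would need only 24 per arm and so does not fit the stated 31.

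**1. Reproducing the sample size.**

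- Normal formula: n = 2 × [SD × (1.960 + 0.842) / difference]² = 2 × [5.5 × 2.802 / 4]² = 29.7, so 30 per arm.
- Two-sample t test (noncentral t): power is 79.1% at 30 per arm and 80.4% at 31. The smallest sufficient number is 31, which is the stated figure.
- Allowance: 31 × 1.10 = 34.1, taken as 34 per arm and 68 in all, as stated.

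**2. True size of the Z test with an estimated SD.** With equal arms and a common SD, df = 2n − 2 and the size is 2 × P(t_df > 1.96).

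| Children per arm | df | True two-sided size | Correct critical value |
|---|---|---|---|
| 34 | 66 | 5.42% | 1.997 |
| 31 | 60 | 5.46% | 2.000 |

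A simulation of one million trials per setting (normal data, equal SDs) gave about 5.4% in both cases.

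**3. Intervals, if any were reported.** The ratio of t to normal half-widths is 1.997/1.960 = 1.019 at 34 per arm and 2.000/1.960 = 1.021 at 31. A normal-based interval would thus be about 2% too narrow, with coverage of 100 − 5.42 = 94.6% or 100 − 5.46 = 94.5%.

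**4. How often it would matter.** Under no effect, the absolute statistic falls between 1.96 and the t critical value with probability 5.42 − 5.00 = 0.42% (34 per arm) or 5.46 − 5.00 = 0.46% (31 per arm).

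**5. After the change.** A t reference gives 5.00% under the same assumptions. Power at 31 per arm is the 80.4% from step 1.

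**The case against.** The strongest reply is that the label is loose wording in a condensed article. No critical value or variance estimator is printed, the sample size matches a t test exactly, and the regression fallback would normally give t-based results anyway. The statistician may well intend a t test. That is possible, but the test named is still a Z test, and it is the default analysis. If a t test is intended, the edit simply makes the text say so.

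It is also fair to say that the consequence is very small. That stands, and it sets the weight of the point.

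Several stronger readings are tempting, and the article does not support them:

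- **An error of 5.6%.** At 31 to 34 per arm with a common SD this is not reached. It needs figures that the article does not give: 25 per arm in the per-protocol set (5.58%), 20% missing information with the 15 imputations (5.62%), or one SD twice the other (5.66% at 31 per arm, 5.58% at 34).
- **That the plan's 95% intervals are too narrow.** No confidence interval is planned anywhere in the article, so the remark is conditional.
- **That the sample size is wrong for the named test.** Planning 31 where the normal formula asks for 30 is no defect. It only shows that the t test costs nothing.
- **That the imputation section is deficient because it gives no small-sample degrees of freedom.** Such detail belongs in the statistical analysis plan, which is not at hand.

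**Conclusion.** The point holds as a minor one. As written, the default test for the primary and secondary change scores has a true two-sided error of about 5.4% to 5.5%, an excess of roughly 0.4 to 0.5 percentage points over the stated 5%. It alters the conclusion only if the statistic falls between 1.96 and about 2.00. The effect estimate and the sample size are not affected.

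The figures assume a two-sided test at 1.96, independent children, roughly normal change scores, a common SD, and no effect of imputation on the degrees of freedom. Both interventions are delivered in groups. Any dependence between children in the same group is a separate matter, which a change of reference distribution does not address.

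**What to change.** In section {20a}, replace the Z test by a two-sample t test, or by a linear model with t-based inference, for the primary and secondary comparisons. The critical value becomes about 2.00 instead of 1.96.

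The cost is a change of a few words and standard software output. Section {14} needs no change, since 31 per group already gives 80.4% power with a t test. The article reports that children were still taking part in groups when it was written, and that analysis waits until all visits are complete. On that account the wording could be settled before the outcome comparison is run.
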